**Fig 10 pone.0302886.g010:**
[figure not shown]
Visual display of the percentage choosing equivalence at each group size comparison.

We will categorise respondents into seven classifications for each context according to their preferences as set out in Table 3.

**Table 3 pone.0302886.t004:** Preference classification based on PTO responses.

Classification	Threshold
Extreme preference for younger age group	Prefers to treat 1 younger age group than 100 older age group
Strongly prefer younger age group	Equivalence group size between 1 and 50 of younger age group equivalent to 100 of the older age group
Weakly prefer younger age group	Equivalence group size greater than 50 of younger age group equivalent to 100 older age group
Equal preference	Expresses equivalence when group sizes are the same or prefers to treat 100 of not preferred age group than 95 of the preferred age group
Weakly prefer older age group	Equivalence group size greater than 50 of older age group equivalent to 100 younger age group
Strongly prefer older age group	Equivalence group size between 1 and 50 of older age group equivalent to 100 of the younger age group
Extreme preference for older age group	Prefers to treat 1 older age group than 100 younger age group

Multinomial logistic regression analyses will be used to explore whether the individual’s classification from their PTO responses (either based on Table 3 or simplified to three classifications) is associated with respondent characteristics and the age/context of the PTO question. This will treat the within childhood age comparisons (that are included in the chaining tests) separately to comparisons between children and adults.

Controls will include ages used in the PTO question, type of health gain, respondent demographic characteristics, and methods factors (whether the younger age appears on the left or right of the screen, forced or unforced preference). Alternative approaches to addressing the fact that individuals complete more than one PTO question will be explored including clustering standard errors and random effects multinomial logistic models.

#### 2.7.4 Comparing PTO values to attitudinal questions

We will present the percentage of potentially inconsistent responders based on the rules in Table 4. These will be interpreted cautiously as there may be legitimate reasons for apparent contradictions.

**Table 4 pone.0302886.t005:** Identification of potentially inconsistent responders.

	Which of these statements best reflects your views?	Potentially inconsistent responses
1	For medical care that improves quality of life temporarily, children should have some priority over adults.	For any of the 3 quality of life questions relative weights suggests equal value or a pro-adult preference.
2	For medical care that improves quality of life temporarily, adults should have some priority over children.	For any of the 3 quality of life questions relative weights suggests equal value or a pro-child preference.
3	People should have the same priority with respect to medical care that improves quality of life temporarily, regardless of age.	For any of the 3 quality of life questions relative weights suggests a pro-adult or pro-child preference.
4	For medical care that extends life children should have some priority over adults.	For any of the life extension questions relative weights suggests equal value or a pro-adult preference.
5	For medical care that extends life adults should have some priority over children.	For any of the life extension questions relative weights suggests equal value or a pro-child preference.
6	People should have the same priority with respect to medical care that extends life regardless of age.	For any of the life extension questions relative weights suggests a pro-child or pro-adult preference.
7	This is fair because they are children	For any of the 7 PTO questions relative weights suggests equal value or a pro-adult preference.
8	This would make me feel concerned	For any of the 7 PTO questions relative weights suggests a pro-child preference.
9	This would be unfair	For any of the 7 PTO questions relative weights suggests pro-child preference.

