#### 2.3.7 Group ages

In choosing the ages of children and adults for comparison within the PTO questions several factors were considered, including ease of interpretation, feasible sample size for each age comparison and existing gaps in the literature. The age category ‘newborn’ is often used in studies exploring social value, but this may be a slightly ambiguous category since a small baby a few months old could be described as newborn, as could a baby a few minutes old. A common childhood age used in the literature is 10 years old, therefore including this category would enable a direct comparison of findings. The recent systematic review [11] identified gaps in the evidence base in relation to very young children (<5 years) and young adults (18–24 years). It also identified a non-linear relationship between age and social value (lower for the very young children and adolescents compared with primary school age children) which suggests there would be a benefit to including many different young ages within the study.

The study adopts thirteen age categories (1 month, 2, 4, 6, 8, 10, 12, 14, 16, 18, 20, 22 and 24 years) enabling a reasonable number of respondents answering questions on each age category whilst including sufficient age categories to identify the hypothesised non-linearity of the value of health gain across different ages. The study also seeks to understand the relative preferences held towards health gains for patients as they transition from childhood to adulthood, hence three young adult age categories are also included.

To ensure a reasonable sample size for each age comparison (given the fixed study budget), only two adult ages were used in the main questions (with two other child/youth ages used in the chaining questions). We chose adult ages which would unambiguously be considered ‘adulthood’ but would not evoke issues around health and healthcare in older ages, hence pick up a potential preference to dis-favour very old adults compared to younger adults. In piloting, some respondents prioritised 40 year olds over children due to an assumption that they may have young children as dependents, therefore we complemented this age with an older age, 55 years, which is less likely to be associated with parents of small children.

The social value of health gain to young and middle-age adults versus old adults is outside the scope of this study.

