#### 2.3.11 Testing data quality and the stability of preferences

Internal consistency of responses can be assessed by tests of cardinal transitivity [46], which is also referred to as ratio consistency, multiplicative transitivity or triad consistency. An individual’s PTO equivalence value for ages 10 versus 20 and 20 versus 30, for example, should accurately predict their PTO equivalence value for age 10 versus age 30. To test this at an individual level requires individuals to be asked at least three questions which ‘chain’ together.

Internal consistency may be judged by comparing PTO answers against other methods for eliciting aged-based preferences such as opinion questions and ranking. However, past evidence suggests fairly systematic differences across research methods with ranking more often being linearly related to age, and opinion surveys responses more likely to reflect a preference for equal treatment [11]. Therefore, these indirect comparisons cannot say much about data quality.

This survey will include an attention check question, consistency comparisons to screening data based on personal demographic data and a minimum time to complete, all of which aim to exclude responders who are not engaged with the survey. We will also consider consistency comparisons to attitudinal questions, but these will not be treated as strict quality checks since there may be legitimate reasons for these differences.

A ratio test will be undertaken for one of the years of life extension questions by chaining PTO values. Each respondent will answer the main PTO questions for just one age. For the question relating to life extension of 2 years they will answer two additional chaining questions i) their given age compared to an age which is either higher or lower by 10 years, as shown in Table 1A, and ii) this age compared to aged (40 or 55), as shown in Table 1B. The expected PTO value will be calculated for each individual based on the two PTO equivalence values (Age X vs (40 or 55)) x (Age Y vs (40 or 55)) and this will be compared to the actual equivalence value (Youngest from X or Y vs (40 or 55)). For example, if the respondent is given age 8 for their PTO questions, they will be asked to complete a PTO comparing patients of ages 8 vs (40 or 55). They will also be asked to compare ages 8 vs 18 and ages 18 vs (40 or 55). The product of the last two responses (the expected value) will be compared to the ages 8 vs (40 or 55) response (the actual value).

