#### 2.3.12 Order effects and randomisation of question order

Order effects may arise through learning effects which result in respondents giving more accurate preferences in later questions and through respondent fatigue which may result in less attention being given to later questions. The order of questions may also generate framing effects leading respondents to focus on certain aspects of the choice–for example asking a question about children leading short lives first may lead people into considering length of life even during questions on quality of life. Earlier questions may draw respondents’ attention to differences between temporary versus permanent health gains [47]. Ubel et al., (2001, 2002) [48,49] identified strong order effects in PTO questions both from numerical anchoring from the group sizes in earlier questions and from questions which make people think about equity considerations and avoiding discrimination. To avoid ordering effects, this study will randomise the order of the PTO question, although the survey will avoid switching question types (e.g. between life extension and quality of life improvement) so as not to add to respondent burden. Participants will be randomised to receive either the life extension questions first (4 questions shown in random order) or the quality of life enhancing questions (3 questions shown in random order) first. The attitudinal and opinion survey questions will follow the PTO to try and avoid further focusing effects. We will test the impact of participants seeing life extension or quality of life enhancing questions first.

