**Table pone.0302886.t002:** 

Which of these statements best reflects your views about prioritising different types of health care?			
	Children should have some priority over adults.	Adults should have some priority over children.	People should have the same priority regardless of age
For medical care that improves quality of life temporarily (with no long-term effects)			
For medical care that extends life by a few years			
If the Australian governments were willing to pay more for a treatment for children compared to adults which gave the identical health gain–what would you think? ⚬ This is fair because they are children ⚬ I’m not sure ⚬ This would be unfair			
Which one of these statements best reflects your views about Medicare priorities? ⚬ Medicare should give priority to treating patients who will die young. ⚬ Medicare should give priority to treating patients who will get the largest amount of health benefit from treatment. ⚬ Medicare should give the same priority to treating all patients. Amount of health benefit and whether patients have had a short life is not relevant. ⚬ Medicare should base priority on a combination of treating patients who will get the largest amount of benefit and treating those who will die young. ⚬ Unsure ⚬ None of the above describes my views about Medicare prioritisation.			

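### Table 4 counts an equal-value answer between two young ages as contradicting a child-versus-adult attitude, which distorts the aim 3 inconsistency percentage

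*Protocol article*

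**What the plan says.** Section 2.7.4 sets attitude answers against PTO answers. For respondents who find it fair to pay more for children, row 7 of Table 4 flags the case "For any of the 7 PTO questions relative weights suggests equal value or a pro-adult preference". For those who give children priority in life extension, row 4 flags "For any of the life extension questions relative weights suggests equal value or a pro-adult preference". Row 5 is the mirror image for adult priority. Row 1, on quality of life, uses "For any of the 3 quality of life questions relative weights suggests equal value or a pro-adult preference".

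The attitude items in Box 3 (Section 2.3.17) contrast children with adults; the fairness item asks about paying more for children "compared to adults which gave the identical health gain".

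On the number of questions, Section 2.3.12 says "Participants will be randomised to receive either the life extension questions first (4 questions shown in random order", with three quality of life questions in the other block. Section 2.3.11 adds two chaining questions to the 2-year life extension question. One compares "their given age compared to an age which is either higher or lower by 10 years"; the other compares that second age with 40 or 55. The ages come from the "thirteen age categories (1 month, 2, 4, 6, 8, 10, 12, 14, 16, 18, 20, 22 and 24 years" listed in Section 2.3.7.

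Row 8 refers to the answer "This would make me feel concerned". The three options in Box 3 are that the policy is fair, that the respondent is unsure, and that it is unfair.

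**The concern.** An inconsistency rule should compare an attitude with answers that can contradict it. The question between the assigned age X and its chaining partner Y compares two young people. A respondent can hold that children come before adults and also value a 4-year-old and a 14-year-old equally, without contradiction. Because one qualifying answer out of all the questions is enough, that single answer flags the respondent.

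The percentage flagged is quantitative aim 3 in Box 1. It is also listed among the quality indicators in Section 2.7.2, and inconsistencies between attitudes and PTO answers are taken up in the interviews (Section 2.4.1) and focus groups (Section 2.4.2). If part of it comes from the rule itself, readers cannot tell artefact from real disagreement between principles and choices.

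Section 2.7.3 already treats comparisons within childhood separately from child-adult comparisons in the multinomial regression. Table 4 does not carry that distinction over.

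**Working it through.** **Step 1: reproduce the count of seven.** Each respondent answers X vs 40/55 in five contexts (2-year extension, 5-year extension, pain, mobility, distress). The chaining test adds X vs Y and Y vs 40/55, so 5 + 2 = 7. By block, life extension has 2 + 2 = 4 and quality of life has 3, and 4 + 3 = 7. This matches Table 4 and Section 2.3.12. Without X vs Y the count is 6, so row 7 as written includes it.

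**Step 2: list the pairs.** Table 1 sets Y = X + 10 for X up to 12, and Y = X − 10 for X of 14 or more.

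| X | Y | X vs Y, cut-off 18 | 18–24 vs 40/55 also asked? |
|---|---|---|---|
| 1 month, 2, 4, 6 | about 10, 12, 14, 16 | two minors | no |
| 8, 10, 12 | 18, 20, 22 | minor vs 18–24 | yes, Y vs 40/55 (1 question) |
| 14, 16 | 4, 6 | two minors | no |
| 18, 20, 22, 24 | 8, 10, 12, 14 | minor vs 18–24 | yes, X vs 40/55 (5 questions) |

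X and Y are never above 24.

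**Step 3: apply the rules** to a respondent who prefers the child group to the adult group in every comparison and gives equal value within each group.

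- *Only 40 and 55 are adult.* X vs Y is always young vs young, so it is always answered as equal. Rows 4 and 7 flag 13 of 13 assignments and row 1 flags 0 of 13.
- *Adult means 18 or older.* X vs Y compares two minors in 4 + 2 = 6 of 13 assignments. The other 3 + 4 = 7 contain an 18–24 vs 40/55 comparison. No assignment contains both kinds. Rows 4 and 7 flag 6 + 7 = 13 of 13, but only if the respondent is indifferent both between minors and between adults. Indifference between minors alone gives 6 of 13; between adults alone, 7 of 13. Row 1 flags 4 of 13 (X = 18 to 24).
- *Rules limited to questions that compare a child with an adult:* 0 of 13 under either definition.

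**Step 4: can equal value be recorded in both arms?** Yes. In the unforced arm the respondent chooses equivalence at 100 vs 100. In the forced arm, note b of Table 2 assigns weight 1 to someone who picks 100 over 90.

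**Step 5: the other rows.** Rows 3 and 6 concern equal priority at any age. Equal value is the consistent answer there, and a preference in X vs Y is a genuine contradiction. Rows 8 and 9 flag only a pro-child preference, a term Table 4 does not define for two young ages.

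**The case against.** The strongest case is that little depends on this. Table 4 labels respondents only as potentially inconsistent, and Section 2.7.4 promises cautious reading. Section 2.3.11 says these comparisons are not strict quality checks. Section 2.7.2 specifies sensitivity exclusions for rapid completion and low comprehension, not for this flag. All of that stands: the ratio of means, the median of individual ratios and their intervals do not change. It limits the consequence but does not correct the percentage named in aim 3.

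It can also be said that rows 4 and 5 mean only the main life extension questions. Their wording leaves this open; the explicit number in row 7 does not.

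Several stronger readings are tempting and not supported:

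- *All respondents who favour children will be flagged.* The 13 of 13 depends on a specified preference pattern, and the documents do not say how common it is.
- *Quality of life row 1 is wrong for 4 of 13 ages.* This requires ages 18 to 24 to be adults. Section 2.3.7 calls them young adults, but Box 1 sets ages 0 to 24 against an adult of 40 or 55, and on that contrast the figure is 0 of 13.
- *X vs Y should leave the whole table.* Rows 3 and 6 need it.
- *Random slips inflate the any-question rule by a known amount.* The documents give no slip rate.

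**Conclusion.** The point holds for row 7 as written, and for rows 4 and 5 if they cover all four life extension questions. An equal-value answer between two ages of 24 or younger is counted against an attitude that it does not contradict. For the respondent described, with only 40/55 as adult, rows 4 and 7 flag all 13 assignments. With a cut-off of 18, six assignments are exposed through two minors and seven through 18–24 vs 40/55. The assumptions are the question set in Table 1 and Section 2.3.12 and the stated preference pattern. The effect on the actual sample percentage cannot be estimated from the documents.

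Row 8 is a separate, plain mismatch with Box 3. If unsure respondents were mapped to it, any pro-child answer would make them inconsistent; the text does not say that they will be.

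This is worth correcting before analysis. It concerns one descriptive result and leaves the social value weights alone.

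**What to change.** 1. Exclude X vs Y from rows 4, 5, 7 and 9, and from row 8 if it is kept. Replace the seven in those rows by the number of eligible questions: six in rows 7 to 9, and three life extension questions in rows 4 and 5, before any restriction on ages 18 to 24.
2. Keep all questions for rows 3 and 6.
3. For rows 1, 2, 4, 5, 7 and 9, state whether ages 18 to 24 count as children. Report the percentage with and without the 18–24 vs 40/55 comparisons, with denominators.
4. Delete row 8, or state that an unsure answer is not classed as inconsistent.

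The cost is a reworded table and a filter in the analysis code; data collection is unchanged. The downside is fewer eligible questions per respondent. When 18–24 comparisons are dropped, rows 7 and 9 rest on six questions for X up to 6 and X = 14 or 16, on five for X = 8 to 12, and on one (Y vs 40/55) for X of 18 or more. The last group, 4 of 13 assignments or about 31%, also leaves rows 1 and 2. With equal allocation of the target 2000 that is 2000 × 4/13, about 615 people. A flag based on one question is not comparable with one based on six, so the denominators must be shown.

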**Table 1 pone.0302886.t001:** a. A given age compared to an age either higher or lower by 10 years. b. Age Y (values from Table 1a) compared to age (40 or 55).

Age		Ages used in the PTO for life extension of 2 years		
X		Randomly chosen from one of 13 ages (1 month to 24)		
Y		Age X plus 10 years if X < = 12 OR Age X minus 10 years if X > = 14		
	Expected value		Actual value	
If X is the youngest age	(Age X vs Y) x (Age Y vs (40 or 55))		X vs (40 or 55)	
If Y is the youngest age	(Age Y to X) x (Age X to (40 or 55))		Y vs (40 or 55)	

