We will explore the uncertainty around the ROM and MOIR using bootstrapping of the pairs of assigned values described above. We will use 1000 replications with replacement to calculate the percentile confidence interval (CI 2.5%, 97.5%). Other approaches will be explored depending upon the skew of the bootstrap data.

The data collected alongside the qualitative interviews will be combined with the main dataset.

Results of the test of chaining of responses will be considered by comparing the predicted equivalence value (from the chained PTOs e.g. age 2 vs age 12 and age 12 vs age 40) to the related actual equivalence value (e.g. age 2 vs age 40). The predicted (from chained PTO questions, see Table 1A) and actual values will be shown in a scatter plot. We will categorise respondents into meeting or not meeting the chaining test based on whether they display a preference reversal or if the estimate equivalence group size and the actual group size have a difference of 20 or more people (alternative thresholds will be considered). We will use logit regression to explore whether not meeting the chaining test is related to respondent characteristics or other indicators of data quality.

For each age comparison, we will report ratio of the means and median of the individual ratios, for the 5 health contexts. T-tests will be used to determine if the mean of the ratios is statistically significant different between two study arms (offering a choice of equivalence vs not offering the choice of equivalence), and Wilcoxon’s U-test will be used to determine if median values are statistically significantly different between two arms. An example of how the data will be presented is shown in S4 Table. T-tests will be used to determine if the mean of the ratios value is statistically significantly different between two contexts comparing a health gain of 5 years versus 2 years, and Wilcoxon’s U-test will be used to determine if median values are statistically significantly different. Kruskal-Wallis H tests will be used to determine if the ratios are statistically significantly different between the three contexts across relieving pain, mobility problems and emotional problems.

We will produce histograms showing the distribution of equivalence values for each age comparison; combined, and separately for the forced (dichotomous) and unforced (offering equivalence choice) modes.

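### Table 4 checks child-versus-adult attitudes against a chaining question that compares two young ages, so some consistent respondents are flagged as potentially inconsistent

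*Protocol article*

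**What the plan says.** The attitude items in Box 3 (section 2.3.17) ask about children as against adults. Table 4 (section 2.7.4) compares them with the PTO answers. Row 7, for respondents who find paying more for children fair, flags them on this condition: "For any of the 7 PTO questions relative weights suggests equal value or a pro-adult preference". Row 4, for those who give children priority in life extension, uses: "For any of the life extension questions relative weights suggests equal value or a pro-adult preference". Row 5 is the mirror image for those who give adults priority.

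Section 2.3.12 gives the question count: "life extension questions first (4 questions shown in random order) or the quality of life enhancing questions (3 questions shown in random order) first". Section 2.3.11 explains why there are four life extension questions: "For the question relating to life extension of 2 years they will answer two additional chaining questions". These are X vs Y and Y vs 40 or 55, with Y set in Table 1 as "Age X plus 10 years if X < = 12 OR Age X minus 10 years if X > = 14".

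For the multinomial regression, section 2.7.3 makes a distinction that Table 4 lacks: "This will treat the within childhood age comparisons (that are included in the chaining tests) separately to comparisons between children and adults".

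The flagged percentage is quantitative aim 3 in Box 1. It is also one of the quality indicators to be reported under section 2.7.2.

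**The concern.** An attitude about children versus adults says nothing about how a 4-year-old compares with a 14-year-old. Someone who puts children before adults and sees no difference between those two ages is fully consistent. Rows 4 and 7 still flag that person, because one of the scored questions suggests equal value. Row 5 does the same to someone who puts adults before children.

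The study sets out to measure and explain conflict between attitudes and PTO answers: it is quantitative aim 3, qualitative aim 2, and a topic for the interviews and focus groups. If part of the reported conflict comes from the scoring rule, a reader of the percentage cannot separate it from real disagreement.

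**Working it through.** **1. Which questions are the seven?** Life extension: X vs adult at 2 years, X vs adult at 5 years, X vs Y, and Y vs adult, which makes 4. Quality of life: X vs adult for pain, mobility and distress, which makes 3. The total is 4 + 3 = 7, the number in Table 4. Without the chaining questions it is 2 + 3 = 5, which agrees with the reporting plan in section 2.7.3 "for the 5 health contexts". So the seven include both chaining questions.

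**2. Test respondent.** Take someone who prefers any child to any adult and is indifferent within each class. Indifference is scored as equal value in both arms: directly where equivalence is offered, and through footnote b of Table 2 (weight 1) under forced choice.

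**3. Why a flag is certain.** X vs Y, Y vs adult and X vs adult are all three pairs that can be formed from three ages. With only two classes, at least one pair must fall within a single class. That pair is valued equally and triggers rows 4 and 7. By symmetry, row 5 flags the adults-first respondent.

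**4. Enumeration at a cut-off of 18**, with Y from Table 1:

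| Assigned X (Y) | Pair within one class | Ages |
|---|---|---|
| 1 month (10), 2 (12), 4 (14), 6 (16), 14 (4), 16 (6) | X vs Y: no adult | 6 |
| 8 (18), 10 (20), 12 (22) | Y vs 40/55: no child | 3 |
| 18 (8), 20 (10), 22 (12), 24 (14) | X vs 40/55: no child | 4 |

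6 + 3 + 4 = 13 of 13 ages. The result was also 13 of 13 at cut-offs of 12, 14, 16, 19, 20 and 25, and for both adult ages. At a cut-off of 25, X vs Y alone accounts for all 13, since X is at most 24 and Y at most 22.

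**5. What is left after a change**, for the same respondent under row 7 (number of assigned ages flagged, of 13):

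| Cut-off | As written | Drop X vs Y only | Main X vs 40/55 only |
|---|---|---|---|
| 16 | 13 | 9 | 5 |
| 18 | 13 | 7 | 4 |
| 20 | 13 | 5 | 3 |
| 25 | 13 | 0 | 0 |

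If only the main questions are scored and X is below the cut-off, the count is 0 (0 of 9 ages at a cut-off of 18).

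**6. Row 1 for comparison.** This row uses only quality of life questions, which are all X vs adult. It flags the test respondent for 4 of 13 ages (31%) at a cut-off of 18 and for none at 25.

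**The case against.** Five points can be made for the plan.

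- **The test respondent is stylised.** Someone who favours the younger group in every pair is not flagged if pro-child is read as pro-younger. This stands: 13 of 13 is a share of assigned ages for one type of preference, not a share of respondents. It is also fair that section 2.3.7 expects value to vary across the young ages, so flat preferences within childhood may not be typical. That variation does not rescue the rule, though. Section 2.3.7 describes lower value for very young children than for those of primary school age. A respondent who prefers the older child in X vs Y would also be flagged if that answer is coded as favouring the older side.
- **Y vs 40/55 is mostly a proper child-versus-adult question.** This stands. It always contains an adult, and at a cut-off of 18 it contains a child for 10 of 13 ages. X vs Y itself spans 18 for 7 of 13 ages. A reader might infer that both chaining questions are always off the point; they are not.
- **Ages 18 to 24 may belong on the child side.** Box 1 sets 0 to 24 against an adult of 40 or 55, and section 2.5.2 calls all 13 ages childhood or youth groups, while section 2.3.7 calls 18 to 24 young adults. The protocol is ambiguous here, so scoring those ages is not in itself a demonstrated error. The main point survives either way: if everyone up to 24 is a child, X vs Y never contains an adult.
- **Rows 4 to 6 give no number.** They could be meant to cover only the main life extension questions. That is possible but is not what they say, and row 7 fixes the count at seven.
- **The consequences are limited.** The label is hedged, cautious interpretation is promised, and section 2.3.11 says these comparisons are not strict quality checks. This stands as a limit on severity. It does not remove the artefact: the caution concerns legitimate reasons behind apparent contradictions, and here nothing contradicts the statement.

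**Conclusion.** The point holds for rows 4, 5 and 7. As written, they score child-versus-adult statements on a question that section 2.7.3 itself sets apart from child-versus-adult comparisons. A respondent with a strict two-class view is flagged for all 13 assigned ages, wherever the line is drawn.

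Two stronger readings are not supported. First, it does not follow that everyone who prioritises children will be flagged. The protocol does not say how common the two-class view is, and consistent favouring of the younger group can escape the flag, so the overall inflation cannot be quantified. Second, the PTO results are not compromised. The flag excludes nobody and enters no ratio of means, median, confidence interval or comparison between arms.

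The damage is confined to the aim 3 percentage and the matching indicator in section 2.7.2. It should be corrected before analysis, but it does not threaten the study's main estimates.

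**What to change.** In Table 4:

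- Remove X vs Y from the child-versus-adult rows 4, 5 and 7, and from rows 8 and 9 for coherence. Rows 8 and 9 flag only pro-child answers, so indifference on X vs Y does not trigger them.
- Score these rows on the main X vs 40/55 questions: the two life extension questions for rows 4 and 5, and all five for rows 7 to 9, replacing the count of seven by five. Dropping X vs Y alone is not enough at a cut-off of 18, where 7 of 13 ages would still be flagged for the test respondent.
- State whether ages 18 to 24 count as child or adult for this table. Report respondents assigned 18, 20, 22 or 24 separately, with the denominator for each row. At a cut-off of 18 the main questions contain no child for these 4 of 13 ages (31%), and this affects row 1 as well.
- Leave rows 3 and 6 on all their questions. Equal priority regardless of age does apply to two young ages.

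The cost is new table wording and a filter in the code, applied to data that will be collected anyway. The small downside is that fewer questions are scored per respondent and the results for ages 18 to 24 are shown apart.
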